#### Cognitive impairment

Cognitive impairment was assessed with the Mini-Mental State Examination (MMSE)
[41]. The MMSE contains 30 items and the score ranges from 0–30. For those participants who were not able to do one or more parts of the MMSE questionnaire, for example because of blindness, the maximum total score was reduced accordingly (n = 14). A few participants were unable to write, and hence were allowed to dictate the sentence. No reductions in scoring were made because of this.

#### Depressive symptoms

Depressive symptoms were assessed with the 20-item Centre for Epidemiologic studies Depression Scale (CES-D)
[42]. The CES-D scale is a widely used self-report measure in community samples. Its reliability and validity has been demonstrated in heterogeneous samples
[55]. The participant rated the frequency of each depressive symptom during the previous week. Each item is scored from 0 to 3 with higher scores indicating more depressive symptoms (total score range 0–60). For participants with one missing item, the total score was calculated (n = 15). In the CES-D scale, the cut-off score indicating the presence of clinically important depressive symptoms in community populations is 16 or more
[56].

#### Sensory functions

Perceived sensory functions were assessed using a structured questionnaire. Participants’ near and distance vision, with eyeglasses if needed, were evaluated using three questions with three-point rating scales. Furthermore, the interview included a question about possible limiting effects of vision on participants′ mobility
[43]. Different aspects of hearing ability as well as hearing-aid usage were assessed by 11 questions. The questions were modified from the Hearing Disability and Handicap Scale and they concerned for example the participants^′^ ability to hear in different listening environments, to locate the sound source and the avoidance of social situations because of the possible hearing difficulties
[57,58]. Hearing- and vision-related questions were selected for this study based on the findings of the previous large-scale Finnish studies
[44,59,60].

#### Perceived postural balance and falls

Perceived postural balance was assessed with the question: “Are you dizzy or do you suffer from poor balance?” The response options were: 1) rarely or never, 2) sometimes, causing me some distress, and 3) often, causing me much distress. Fear of falling was assessed by the question: “Are you afraid of falling?” The response options were: 1) never, 2) occasionally, 3) often, and 4) constantly
[44]. Information on falls (“Have you fallen or slipped during the previous year?” yes/no) and injurious falls (“If yes, how many times you needed physician’s treatment?”) during the previous year was also collected.

#### Interviewer-rated functional status

At the end of the face-to-face interview, an eight-item questionnaire from the Health 2000 project was used for the interviewer-rated assessment of functional status of the participant. The questionnaire includes assessment of mobility, daily activities, vision, hearing, use of hearing aid, ability to talk, ability to understand speech, and temporal disability
[45].

### Personal goals

The content of personal goals was studied using a revised version of Little’s (1983) Personal Project Analysis
[46]. The following instruction was used in the interview: “We all have different goals that we try to accomplish in our daily lives or achieve in the future. The goals may be related to any life domain, such as hobbies, daily life, health, family or friends. Think about the goals you have in your life at the moment. The goals can be big or small as long as they are important to you”. If the participant did not understand the question, examples of the personal goals of a young person were given. Participants were asked to mention as many personal goals as possible; the number of goals mentioned ranged from zero to seven. These personal goals will be classified by two independent assessors in 22 categories based on their content using a coding scheme developed for the purposes of the study (revised on the basis of the coding scheme used by Salmela-Aro et al. 2009
[61]). Any disagreements between the two assessors will be discussed until total agreement is reached. A participant may have goals in several different categories or several goals in the same category. Eventually, each personal goal category will be coded on a dichotomous scale with zero indicating no goals and one indicating at least one goal in the respective category. Those with no personal goals will be coded separately in a category labeled no personal goals.

Personal goals are defined as states that people strive to achieve or avoid in the future
[46] . Research on personal goals among people aged 75+ is limited (e.g.
[62]), although setting and pursuing relevant personal goals might affect older adults’ functioning and quality of life in old age.

### Relocation and other major life events at follow-up

At the one- and two-year follow-up interview participants will be asked about major life events since the previous assessment (one year ago) in a semi-structured interview. Major life events, such as those related to health (e.g. new medical diagnoses, worsening or recovery of an existing illness), to mobility (e.g. new mobility problems, or new assistive devises), to the family situation (e.g. death of a spouse) or to living situation (e.g. relocation), and to leisure activities (e.g. new or ended hobbies) may affect life-space mobility.

Participants who have relocated will be asked to give their consent to a short face-to-face interview and evaluation of the entrance and exterior surroundings of their new home with the HE Screening Tool. In this way, we aim to capture changes in the environment and their possible effects on the size of the life-space. The face-to-face interview will also include questions about the reasons for relocation and the related decision making process, and the environmental barriers and facilitators of the new living environment.

### Substudy

A substudy on habitual walking and life-space was conducted in the week following the LISPE baseline face-to-face interview.

### Diary

During the face-to-face interview at baseline, every participant was asked if they would be willing to keep a 7-day diary. Those who agreed were asked to maintain their usual daily activities and record them in a structured diary. Participants were instructed to record the life-space level they moved through each day in accordance with the LSA questionnaire
[16]. In addition they listed the places visited. The total time spent outside the home (in minutes) was recorded. In addition, the participants recorded whether unusual events, such as illness or extreme weather, affected their normal daily routines during the day. At the end of the 7-day period, the participants returned the diary to the research center by mail. The life-space diary was developed by an expert group for the current project. Diaries that contained data for more than 4 days and had at most one missing day between two recorded days were considered valid.

### Accelerometer

In the period from March 26^th^ to June 15^th^, 2012, an accelerometer (Hookie, tri-axial, “AM20 Activity Meter”, Hookie Technologies Ltd, Espoo, Finland) was offered to a subgroup of the participants, selected on the basis of interest expressed during the initial phone interview and the availability of accelerometers. The accelerometer was given with detailed instructions provided orally and on paper. In addition to keeping the life-space diary, participants were instructed to wear the accelerometer for 7 consecutive days following the face-to-face interview. They were instructed to wear it over the right side of the waist, over clothing on an elastic belt all day from waking up to the time they went to sleep. It was to be removed only for water activities. Participants were asked to register in their diary the exact time when the accelerometer was put on and taken off. The accelerometer was returned by mail in a foamed envelope. If the participant reported difficulty getting to a post office or mail box, the accelerometer was picked up from the participants’ home.

For the analyses, the default settings for thresholds and formulas for calculating different parameters supplied by the manufacturer will be used. It is possible to obtain the following parameters from the accelerometer: step count, total activity points, average MET (metabolic equivalent of task) and total time spent on different activities (walking, running, low activity and other).

By measuring acceleration (change in velocity with respect to time, m/s^2^) of the body, it is possible to obtain an estimate of the intensity of physical activity. Accelerometers have been shown to be useful in monitoring physical activity patterns of community dwelling older people
[63].

### Outdoor temperature

Daily outdoor temperature values were obtained from the local energy company (Jyväskylän Energia Ltd). The daily temperature was a mean value of four measurement points located in different parts of the study area recorded at 1 p.m. Outdoor temperatures were matched with the dates of the diary days.

### Quality assurance

Ten interviewers were recruited from among students in the Department of Health Sciences at the University of Jyväskylä. Interviews were also conducted by two members of the research group (JE, MS). The interviewers received special training before the study started. The training included three days on interviewing techniques suitable for older people, the scales and tests, the criteria for the observational scales, the use of the electronic form for the CAPI, study ethics, safety and the oath of confidentiality. For the objective physical environmental evaluation, the training comprised two days of theoretical and practical training, led by the developer of the HE Screening Tool (SI). A manual of operations was written to standardize the testing procedures.

The CAPI method was used as its advantages include a lower risk for errors and missing data, no separate data entry phase, and availability of data immediately at the end of the data collection phase
[64]. The interviewers returned the forms and interview data on a USB memory stick during their weekly visit to the research center. At this time, the material was checked and any unclear issues were discussed. Data saved on the laptop and USB memory stick was blinded in terms of the identity of participants. In addition, we organized a seminar for the interviewers to discuss their experiences during the interviews and to assure the data collection was done according to standard. Throughout the data collection phase members of the research team (MR, EP, [name], MK) monitored the quality of the data and provided feedback to the interviewers.

### Ethics

The study complies with the principles of good scientific conduct and good clinical practice in all its aspects (Helsinki declaration). The LISPE project was approved by the ethical committee of the University of Jyväskylä, Finland, on November 2^nd^, 2011. The protocol of the study was described in the letter of invitation sent to all the potential participants targeted. During the phone interview and face-to-face interview further information was given and participants were able to withdraw from the study at any point without consequences. Subjects who participated in the face-to-face interview signed a consent form which also included information about the study protocol and measurements. In addition, participants could opt to give permission for the use of register data on health service use and mortality.

### Data management and statistical analysis

#### Statistical analyses

In this study, when inferential analyses are conducted for continuous variables, they will primarily be based on parametric general linear models such as multiple regression and analysis of variance. Markedly non-normally distributed data will be transformed prior to inferential comparisons. For variables that cannot be successfully transformed, nonparametric methods will be used. Categorical variables will be analyzed with logistic regression or categorical response models. If the expected frequencies are too small for asymptotic assumptions, exact testing techniques will be used.

Data will be analyzed using multivariate statistical methods which allow analyses of time-dependent outcomes and covariates. In longitudinal analyses, we will use approaches which take into account mortality as a competing risk for other health outcomes. Person-environment interaction will be analyzed with help of regression analyses. Path modeling and structural equation modeling will be used for multilevel analyses of environmental and individual characteristics relative to the study outcomes. Generalized estimating equations (GEE) models will be used to analyze differences in changes in prevalence over three time points. The level of statistical significance will be set at p < 0.05 (two-sided).

### Data reporting

In all future publications, data will be reported following the STROBE criteria (Strengthening the Reporting of Observational studies in Epidemiology)
[65].

## Results

### Study flow and non-respondent analyses

Figure
2 shows the flowchart of the study. Of the initial sample of 2 550 men and women, 2 269 persons were contacted on the phone to determine their eligibility and willingness to participate in the study. In total, 1 070 persons declined (unwilling n = 551, no time n = 121, poor health n = 398), 304 were not eligible, and 41 persons withdrew their consent between the phone interview and the face-to-face interview. During the face-to-face interview four participants were excluded due to communication problems and the data of two participants were lost due to a technical problem. The total baseline sample size was thus 848. The mean age of the participants was 80.6 ± 4.3 and 62% was women.

**Figure 2 F2:**
[figure not shown]
Flow chart of the study.

In total, 811 of those who declined to participate and 833 of those who participated in the study, responded to the initial phone interview were included in the non-respondent analyses (n = 1644). Those who declined to participate were older (81.2 ± 4.1 vs. 80.4 ± 4.2, Students T-test p < .001), more often lived with a spouse or others (Chi-square test p = .006), more often perceived their health as poor or very poor (p < .001), perceived more difficulties in outdoor mobility (p < .001) and moved outdoors less often than those who participated in the study (p < .001) (Table
2).

**Table 2 T2:** Non-respondent analyses and subgroup analyses

	**Total sample**			**Substudy**			
	**Non-participants**	**Participants**	***Chi-square***	**Accelerometer**	**Diary-only**	**Not in substudy**	***Chi-square***
	(n = 811)	(n = 833)	*P-value*	(n = 170)	(n = 354)	(n = 309)	*P-value*
**Gender** (women)	66.1	62.1	.089	63.5	59.3	64.4	0.367
**Housing type**			.511				0.008
Apartment block	56.7	55.9		49.4	60.7	54.0	
Row house	14.5	16.6		19.4	17.8	13.6	
Semi-detached/ detached house	28.7	27.5		31.1	21.4	32.4	
**Living situation**			.006				0.009
Alone	49.7	53.9		55.3	49.7	57.9	
With spouse	44.2	43.1		44.1	47.7	37.2	
With other person	6.1	3.0		0.6	2.5	4.9	
**Self-rated health**			<.001				0.056
Very good	3.0	5.3		7.1	5.9	3.6	
Good	25.2	32.5		35.2	34.5	28.8	
Moderate	49.9	52.3		52.9	50.3	54.4	
Poor	19.9	9.7		4.7	9.3	12.9	
Very poor	2.0	0.1		0	0	0.3	
**Difficulty in outdoor mobility**			<.001				<0.001
No difficulties	52.5	60.5		67.1	62.7	54.4	
Minor difficulties	30.4	28.9		30.6	28.2	28.8	
Major difficulties	10.6	8.0		2.4	7.1	12.3	
Unable with / without help	6.4	2.5		0.0	2.0	4.5	
**Frequency of outdoor mobility**			<.001				<0.001
Daily	63.5	75.9		84.1	77.1	69.9	
4-6 times/week	15.2	13.0		13.5	13.0	11.0	
1-3 times/week	13.5	8.8		1.8	8.5	12.9	
< once /week	7.9	2.4		0.6	0.3	4.5	

Sample characteristics represented as proportions (%) and tested group differences.

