**Figure 3 F3:**
[figure not shown]
Flow chart of the substudy.

The participants in our substudy groups were somewhat younger than those not participating in the substudy (accelerometer group 80.4 ± 4.2, diary-only group 79.9 ± 4.1, vs. not in substudy 81.4 ± 4.4, ANOVA p <0.001). In addition, the participants in the substudy groups reported less difficulty in outdoor mobility (Chi-square test p < 0.001) and going outdoors more frequently (p < 0.001). Those participating in the diary-only subgroup lived more frequently in an apartment block (p = 0.008), in addition, they more often lived with another person (p = 0.009). The gender distribution and self-rated health were not significantly different between the three groups. Baseline assessment of level of physical activity showed that 36.6% of those in the accelerometer group and 44.4% of those in the diary only group participated in moderate to strenuous physical activity for at least 4 hours a week or in physical exercise multiple times a week compared to 21.0% of those not participating in the substudy (<0.001).

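### The overall three-category p = .006 for living situation is attached to a two-way claim (spouse or others versus alone) for which Table 2 gives p of about .09

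*Protocol article*

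**What the plan says.** Under Results, Study flow and non-respondent analyses, the article compares "811 of those who declined to participate and 833 of those who participated in the study" on data from the initial phone interview. On living situation it states that those who declined "more often lived with a spouse or others (Chi-square test p = .006".

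Table 2 gives living situation in three rows, decliners first and participants second: "Alone 49.7 53.9", "With spouse 44.2 43.1" and "With other person 6.1 3.0". One p-value, .006, stands on the header row of the variable. No p-value is given for any pair of categories or any collapsed version.

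The substudy section uses the same construction. Of the diary-only group it says "in addition, they more often lived with another person (p = 0.009". In Table 2 that value stands on the header row for three groups by three categories.

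The Statistical analyses section fixes the threshold: "The level of statistical significance will be set at p < 0.05 (two-sided".

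**The concern.** A chi-square test on a 2 x 3 table has as its null hypothesis that all three shares are equal in the two groups. It can reject because of any one category. The sentence merges two of the three categories, gives a direction, and attaches the p-value of the unmerged table. The merged contrast has its own test, with 1 degree of freedom, and nothing guarantees that it agrees with the overall one.

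Two features of Table 2 suggest that it does not. The category named first, spouse, differs by only 1.1 points. The category with the clear relative difference, other person, holds only 3% to 6% of each group.

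What is at stake is the description of who is missing from the cohort. A reader would take away, with p = .006, that older people living with a spouse or others are under-represented. The evidence at that strength concerns a much smaller group.

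**Working it through.** **Inputs.** Group sizes 811 and 833 and the percentages are from Table 2; the 0.05 two-sided level is from Statistical analyses. Cell counts are not printed, so they are rebuilt as percentage x n.

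- Decliners: 0.497 x 811 = 403.1; 0.442 x 811 = 358.5; 0.061 x 811 = 49.5.
- Participants: 0.539 x 833 = 449.0; 0.431 x 833 = 359.0; 0.030 x 833 = 25.0.

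Decliners are therefore 403/359/49 or 403/358/50 (alone/spouse/other), depending on where the rounding remainder goes; participants are 449/359/25.

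**Step 1: reproduce the printed .006.** Pearson chi-square = sum of (O - E)²/E, with E = row total x column total / 1644, on 2 df.

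- 403/359/49 versus 449/359/25: chi-square 9.97, p = .0068.
- 403/358/50 versus 449/359/25: chi-square 10.53, p = .0052.

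The printed .006 lies between them, so it is the three-category test.

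**Step 2: see where the chi-square comes from.** For 403/359/49, the pairs of cells contribute: alone 1.41, spouse 0.13, other person 8.44. The last is 8.44 / 9.97 = 85% of the total. For 403/358/50 it is 9.02 / 10.53 = 86%.

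**Step 3: test the contrast that the sentence states.** Not alone: 408 of 811 (50.3%) versus 384 of 833 (46.1%).

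- Chi-square = N(ad - bc)² / product of the four margins = 1644 x (403 x 384 - 408 x 449)² / (811 x 833 x 852 x 792) = 2.92 on 1 df, p = .088. With Yates correction p = .097; Fisher's exact test gives p = .093.
- Difference 4.2 points; SE = √(0.503 x 0.497/811 + 0.461 x 0.539/833) = 0.0246; 95% CI 4.2 ± 1.96 x 2.46 = about -0.6 to 9.0 points.

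**Step 4: each remaining category against the rest.**

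| Category | Decliners | Participants | Difference (95% CI), points | p |
|---|---|---|---|---|
| With spouse | 44.2% | 43.1% | 1.1 (about -3.7 to 5.9) | .63 to .67 |
| With other person | 6.1% | 3.0% | 3.1 (about 1.1 to 5.1) | .002 to .004 |

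The spouse range is for the uncorrected test; the other-person range includes Yates and Fisher variants.

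**Step 5: sensitivity to rounding.** The printed decliner percentages fit no exact integer table at n = 811: 49/811 = 6.04% and 50/811 = 6.17%, and neither rounds to 6.1%. A few missing answers are one possible reason. Over all integer tables that do match the printed percentages, with 795 to 811 decliners and 820 to 833 participants, the three-category p is .0056 to .0076. The alone-versus-not p is .087 to .092 uncorrected and .096 to .103 with Yates. None brings the stated contrast below 0.05.

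**Step 6: the substudy sentence.** Rebuilt counts (alone/spouse/other) are accelerometer 94/75/1 of 170, diary-only 176/169/9 of 354, and not in substudy 179/115/15 of 309.

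- 3 x 3 table: chi-square 13.51 on 4 df, p = .009, which is the printed value.
- Diary-only versus the other two groups combined, not alone: 178/354 (50.3%) versus 206/479 (43.0%), chi-square 4.34, p = .037 (.044 with Yates).
- Same comparison, with spouse: 169/354 (47.7%) versus 190/479 (39.7%), p = .02.
- Same comparison, with other person: 9/354 (2.5%) versus 16/479 (3.3%), p = .50. On this row the highest group is those not in the substudy, at 4.9%.

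**The case against.** The strongest reply is that nothing printed in Table 2 is wrong. The .006 stands beside the whole variable, the text points to the table, and the direction stated is the direction observed. On this view the sentence is a loose summary beside a valid overall test. That stands as far as it goes: the overall test is valid and correctly computed, and the fault lies in the sentence that borrows its p-value. It does not rescue the sentence, because a reader will take a p-value in brackets as evidence for the claim it follows.

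The reply also limits what may be concluded. Four stronger readings are tempting, and the documents do not support them.

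- *The groups are alike on living alone or living with a spouse.* A p-value above 0.05 does not show this. The intervals leave room for about 9 points on not living alone and about 6 on living with a spouse.
- *The substudy claim fails too.* It does not. Alone versus not alone over all three groups gives p of about .10, but that is again an overall test and not the diary-only contrast that the sentence makes. That contrast stays below 0.05.
- *The three-category test rejects too readily.* It would often reject when the shares living alone are equal but the other-person shares differ. That is power against a real difference, not an error rate.
- *Later adjustment would target the wrong characteristic.* The article plans no weighting or adjustment on living situation. Its one selection conclusion under Limitations concerns worse mobility and rests on other rows of Table 2, with p < .001.

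Finally, singling out the other-person category is itself a choice made after seeing the data, on about 74 people (49 + 25), without allowance for multiplicity. It should be worded as a description.

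**Conclusion.** The point holds as a mismatch between the stated inference and the test behind it. The distribution of living situation differed between decliners and participants (overall p = .006). The two-way statement in the text does not have that support: p is about .09, and the 95% interval includes zero. The difference is driven mainly by the small group living with someone other than a spouse.

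In the substudy section the conclusion about the diary-only group survives with weaker evidence than printed, about .04 in place of 0.009. Its wording there also invites confusion with the table row for living with another person, on which the diary-only group is not the highest.

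These results assume unweighted Pearson tests and counts rebuilt from rounded percentages. Every rounding-compatible table examined for the main comparison leads to the same conclusion. The consequence is confined to the description of who is missing from the cohort; sample size, outcome analyses and the mobility-related selection conclusion do not change.

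**What to change.** **Main comparison.** Reword the sentence to say that the distribution of living situation differed (overall chi-square p = .006), mainly because more decliners lived with a person other than a spouse (6.1% versus 3.0%), and that the share living alone did not differ significantly (49.7% versus 53.9%). Take the p-values for the second and third statements from the raw data, not from the reconstruction here, and present the category-level result as descriptive.

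**Substudy.** Either label 0.009 as the overall test of three groups by three categories, or replace it with the diary-only versus rest test of alone against not alone, which should come out at about .04. In either case, say that this group less often lived alone, so that the phrase is not read as the other-person row of Table 2.

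**Cost.** A few cross-tabulations on data already held and two reworded sentences. One contrast now presented as significant would be reported as not significant.
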